### Blinding

All preschools, units at preschools and intervention conditions were given letters for identification. The key to which preschool and unit had which letter combination was only known to the first author and the PI – who were not involved in the actual testing and intervention procedures. As an extra precaution, the data was re-named with new letter combinations prior to being delivered to the data analyst (second author).

The testers were not informed of the randomization results and do not know which preschool had which intervention. However, there is a high risk of leakage as the testers spent a lot of time at a preschool and might overhear children and staff talking, unintentionally giving away clues as to which intervention was used. It was not possible to eradicate this problem completely, but the testers were not informed as to the content of the interventions or the hypotheses of the project at large.

### Interventions

In the study, the experimental manipulation was implemented in the preschools as the three intervention conditions SEMLA, DIL and control. SEMLA and DIL are both believed to enhance executive functions, attention, and early maths skills whereas language and socioemotional skills are more clearly grounded in the SEMLA practice. The different mechanisms at work in the two pedagogical paradigms are described below. The description adheres to the guidelines of the TIDieR checklist for intervention, description and replication [52].

#### SEMLA

SEMLA aims to enhance the child’s attention, executive functions, language, socioemotional skills and early maths skills by means of introducing a creative construction project in a material space filled with inspirational materials for the children to engage with based on their individual curiosity, motivation, and desires. The following components provide the mechanisms for change:Individual and group learning scaffolded by trained preschool teachers. The assumption is that SEMLA will facilitate moments of intense attention during which the child, individually or in groups, will engage with the materials provided. The small group sizes are expected to facilitate the teachers’ focused attention on each child as well as the group and will make it possible for the teachers to scaffold each child’s learning.Socioemotionally supportive learning environment. Teachers in SEMLA are instructed to pay specific attention to the children’s social and emotional development during the intervention by encouraging collaboration and supporting interaction between individual children.An aesthetic, playful, creative and experimental exploration is facilitated by the specific materials that are organized in a specifically assigned room, providing conditions for affectively engaging activities and focused attention. The intervention includes various types of building materials, posters of different types of buildings, and an inspirational booklet with guidelines for the preschool staff. In addition, learning tablets are used to search the Internet and for documenting the ongoing activities (pedagogical documentation). The documentation is revisited during the project in order to maintain focus, reflect on the ongoing learning process, and find inspiration for further development.

The staff was trained for four 3-h evening sessions presenting theory as well as practical exploration and creative involvement with the materials. The intention was to enhance the preschool staff’s pedagogical capacity to scaffold and emotionally support the children’s learning through a learning-by-doing intervention. Supervisors guide the teachers through an explorative project similar to the one the children would be working on in order to provide the teachers with a hands-on experience interacting with the materials.

SEMLA was implemented for 1 ½-hour sessions, 4 days a week during the 6-week intervention period. The overall focus during these weeks was to work with a project investigating “How to live and get around 100 years from now”. With support from SEMLA supervisors, staff transformed a space in the classroom for investigational practices. The space was furnished with a set of creative materials, e.g. building blocks, re-cycled materials, textiles, drawing and painting materials, tools, flashlights etc. Children were taught how to document their activities using a digital camera and an iPad and encouraged to make drawings and ‘write’/articulate instructions on the theme chosen. Teachers participated in the creations and were instructed to encourage and scaffold all children to be engaged in learning activities during the SEMLA sessions, as well as to document individual children’s learning, strengths, and difficulties in the process. The combined work of the group was used to enable further scaffolding.

#### DIL

Digital Individual Learning (DIL) for Body and Mind aims to enhance the child’s early maths skills in terms of number sense and self-regulated learning by ways of brain-training and attention enhancing exercises in combination with training early math [22].

The following components provide the mechanisms for change:A package of 12 activities focusing on body awareness, breathing and attention, administered and implemented by the preschool teachers during circle time each session. In particular, two metacognitive strategies (The Bird Breath and Oh, well I can…) were introduced and trained, separately and in combination with other activities. Different materials such as posters, beanbags, balloons and pinwheels were used in the activities.The digital learning game Magical Garden (MG) focusing early math and number sense administered on-line by the Education Technology Group at Lund University. The main theme of the game is for the child to solve math problems in order to collect water to use for creating a flourishing garden. By solving the problems, early maths skills are expected to improve. In addition, by applying the strategies taught in the body and mind exercises, while playing the game, self-regulation skills are expected to improve. The game includes a Teachable agent (TA), based on a learning-by-teaching methodology [53, 54], encouraging the child to teach the TA early math. The game design and narrative provide rich multimodal feedback motivating the child for embodied interaction with the digital tablet involving affect, cognition and action [55].Teachers scaffold the children’s participation throughout the sessions, supporting self-regulation in terms of focused attention, metacognition and emotional regulation, as well as providing support to solve the mathematical tasks and handle the digital device.

Preschool staff was trained before the start of the intervention for four 2-h evening sessions. The training included theoretical and practical elements, such as the rationale for learning early math before school start, the function of self-regulation and the role of the teacher in terms of scaffolding the child’s learning. Detailed descriptions of the exercises were reviewed and practiced, and the teachers spent time learning to use Magical Garden. Time was also spent planning the implementation of the intervention as part of the daily preschool schedule.

DIL was implemented for 1 h 5 times per week for 6-weeks intervention. Each session began with a group activity where the preschool staff taught the children about “the learning body” in terms of how the brain works, focused attention, breathing and meta-cognitive strategies for enhancing self-regulation. Different aspects of the learning body were trained through specific body exercises such as breathing, balancing a beanbag and focusing attention while being distracted. During 15–30 min per session the children individually played Magical Garden, in total adding up to a minimum of 20 sessions for each child, including at least 15 min effective interaction with the Magical Garden each time. In order to avoid distractions and enhance the individual nature of the activity the children wore headphones.

#### Control

The children at the control preschool units had business as usual during the 6 intervention weeks. However, in order to motivate preschool staff at the control units, this group was given BRUK, a self-evaluation tool developed by the Swedish National Agency for Education [2]. BRUK is adapted for different levels of the school system and the version used applies to the preschool setting. The tool is divided into four areas of investigation: 1) Each preschool’s development; 2) Norms, values, and influence; 3) Knowledge, development, and learning; and, 4) Transit, collaboration, and the surrounding world. Each area includes a number of indicators, and each indicator contains criteria that the preschool staff has to evaluate in relation to the work at the preschool. Examples of criteria are: criteria for goal fulfilment; criteria for implementation; criteria for operational conditions.

The work with BRUK was administered by the preschools themselves. A head of school introduced the tool to all staff at the control preschool units. Two areas were chosen to focus on in particular: “the learning environment”, and “routines at the preschool”. The areas and indicators are listed in an on-line formulary, with rating scales indicating Agree completely – Agree mostly – Agree to some extent – Do not agree. The pedagogical staff filled in a form of their own, before having discussions at group level. As areas of improvement were identified the group continued with elaborating methods to improve the quality with the aid of an experienced external preschool teacher. Six months later, a follow-up BRUK was conducted where the improvements were evaluated.

### Adherence

For the SEMLA intervention, implementation fidelity was monitored continuously. After each session the teachers documented which children had participated, whether they had worked mostly together with another child/children or alone, which activities had been undertaken, and whether anything out of the ordinary had occurred. At each preschool unit, one researcher supported and supervised the implementation during regular visits once per week. At these occasions, the sessions were video-recorded, providing rich data capturing the quality of the intervention implementation. Children were encouraged to participate, but were always allowed to opt out or discontinue participation at any time.

For the DIL intervention, objective adherence was registered by the software in terms of the amount of time a particular child had spent playing the game. Once a week, sessions were also recorded by a researcher, providing additional information about the participation of the individual children. During the entire intervention, program support for Magical Garden was provided by the researchers in the Education Technology Group in Lund in order to fix bugs and other potential problems related to the software. The software was upgraded continuously as problems were identified. Children were encouraged to participate, but were always allowed to opt out or discontinue participation at any time.

For the control group, adherence to the BRUK self-evaluation was not monitored other than by the preschools themselves.

### Preschool quality

Preschool quality was estimated on the basis of the ECERS-3 [56]. The rating scale measures process quality in the interactions between staff and children. This is assessed primarily through observation by trained and accredited observers/raters, who in this case were hired from the University of Gothenburg. The Early Childhood Environment Rating Scale is an internationally established tool for measuring preschool quality developed on comprehensive and global definitions of quality and have been found to be more predictive of children’s learning than structural factors such as group size, staff to child ratio, and costs [57]. A quality program must provide a satisfying degree of protection of health and safety, building positive relations, opportunities for stimulation and learning from experience http://ers.fpg.unc.edu/. The third edition consists of 35 items organized into 6 subscales: Space and furnishing, personal care routines, language and literacy, learning activities, and interaction. These are rated from 1 to 7. Minor adaptions of the ECERS-3 scale have been made to the Swedish context, which do not affect international comparison on the whole.

### Data collection

Pretest measurements were collected during a two-week period prior to the intervention period, and posttest measurements during a two-week period directly following the intervention period. Data collection consisted in behavioural testing, on the one hand, and participation in the ERP-experiment, on the other. Only a sub-sample of the children conducted the ERP-experiment.

### Behavioural testing

The behavioural testing was conducted by trained research assistants employed in the project.

Each child was tested twice during the pretest period and twice during the posttest period. Each session lasted between 20 to 40 min. The testing sessions were video-recorded in order to i) allow for validation of testing procedure, and ii) give interactional data on verbal and nonverbal behaviour as the child interacted with the test leader. The tests performed during the first session with each child were, in the order of testing: Dimensional Change Card Sorting (DCCS); Test of Emotional Comprehension (TEC); Bus Story (pretest)/Frog Story (posttest); Maths test; Head, shoulder, knees, toes (HSKT). At the second session, usually taking place the following day, the tests performed were: The Flanker Fish Task; What’s Wrong Cards; Peabody Picture Vocabulary Test (PPVT); Digit Span. The order of the tests was chosen to keep the two sessions equal in length, test different abilities and end sessions with more enjoyable tests (based on opinions of children in a pilot study), potentially leaving a memory of a fun experience for the children. The identical set-up for tests and order of tests were applied at the posttesting period except for two of the language tests: the narrative retell-test exchanged Bus Story to Frog Story and the three What’s Wrong Cards used at pretesting were exchanged to different ones for the posttesting. In both cases, the reason for change was to avoid the child remembering verbatim parts of the story/picture already heard and told.

### The ERP experiment

To measure auditory selective attention, we used a dichotic listening paradigm adapted to children [58] in which auditory test probes are embedded in two different stories, one attended and one unattended. We created a Swedish version of this paradigm called Swedish AUDAT. Test probes were linguistic, the syllable “Ba”, or non-linguistic, a ‘Bz’-like noise created by scrambling short segments of the linguistic probe. Approximately 500 probes were presented while the children attended stories. The ERP responses to probes were later compared between those embedded in attended and unattended stories (see outcome measures). The experiment was conducted by two researchers from the project and was carried out on site in a quiet room at the preschools using a mobile lab setup. EEG was recorded with an Active-two amplifier (BioSemi, Amsterdam, Netherlands) using 16 head channels in a cap, and 6 external channels (mastoid reference electrodes, and electrodes monitoring blinks and eye movement). Participating children had been oriented about the experiment and equipment previously. They were greeted and seated on a small chair where the cap and external electrodes were applied. They were instructed to pay attention to one of two simultaneous played stories presented via speakers. Pictures from the attended story were displayed on a laptop. Each recording session consisted of two story pairs. After each story, the children were asked questions about the attended story to ensure that they did attend. Each session lasted approximately 30–40 min.

### Outcome measures

In the study, we used multiple measures of the children’s attention/executive functioning skills, on the one hand, and their language and communication skills, on the other. These individual measures form the basis for composite measures of executive functioning, and language and communication, respectively. Early maths skills and socioemotional skills, on the other hand, were measured with two individual measures. In the following section, we describe the individual outcome measures and then the composite measures. We then present the background variables of the study.

#### Selective attention

Selective attention was measured using the Swedish AUDAT paradigm, as differences between ERP-responses to attended and unattended probe sounds. In the paradigm the following variables were manipulated (in order of importance): 1. Attending story to the left or right according to instructions and as a function of this also attending probes to the left or right. 2. Linguistic content in probes (“Ba” versus “Bz”). 3. Pause length between probes (200 ms, 550 ms, 1000 ms). 4. Characteristics of attended and unattended story (story content, story voice). To enhance contrast, story pairs played simultaneously always consisted of one female voice and one male voice. The order of probes and pauses was randomized. The order of attention direction, and selection of voices and stories was randomized and balanced over participants.

#### Measures of executive functioning

The components of executive functions can hardly be assessed in isolation, since the targeted cognitive process must be embedded in a certain task context that is likely to trigger other executive functions [16]. Children’s executive functions were therefore assessed using the following battery of tests: 1) The Dimensional Change Card Sort (DCCS), which mainly assesses the child’s cognitive flexibility [59, 60], 2) The Flanker Fish Task [40, 61, 62], which mainly assesses the child’s ability to suppress responses that are inappropriate in a particular context, 3) The Head-Shoulders-Knees-and-Toes (HSKT) test [63], which reflects the child’s ability to inhibit dominant responses of imitating the examiner and also puts high demands on working memory and focused attention, and 4) Forward and Backward Digit Span [64] which assesses short-term memory and working memory. The DCCS and the Flanker task were delivered via a tablet, but verbal instructions were given by the examiner, since there is no available Swedish-speaking tablet version. Results from a recent meta-analysis of DCCS indicate that the test format should not matter [59].

#### Measures of language

In order to assess the children’s receptive vocabulary skills, we used The Peabody Picture Vocabulary Test (PPVT) [65]. The PPVT has not been standardized for Swedish, but is widely used in Sweden, both clinically and in research. The lack of standardization entails that the psychometric qualities of the test are unclear. Hence, only raw scores were used for analysis. In addition to the PPVT test, the following measures related to language were also derived from children’s narratives: 1) lexical diversity (type:token ratio), 2) information score, i.e. how many events the child included in the narratives, 3) syntactic complexity, defined as number of subordinate clauses, 4) morphological complexity, defined as amount of well-formed utterances, and 5) text length, defined by total number of clauses [66].

#### Measures of communication

Communication was defined as the ability to interact in an age-adequate manner. The following behaviours were rated as either 0 (not adequate behaviour for the child’s age) or 1 (adequate behaviour for the child’s age): gaze (meeting eyes while speaking, following gaze and pointing instructions from the tester), gestures (use of complementary and/or supplementary gestures to convey or clarify verbal utterances), body posture (an at-ease appearance rather than fidgeting on the chair etc.), fluency/prosody (speaking up rather than whispering or holding objects/hands to the mouth), following instructions (cooperative versus uncooperative behaviour), turn-taking (adequate turn-taking behaviour rather than interruptions, silence, etc.), and initiative/curiosity (whether the child takes his or her own initiative in the interaction or not). The ratings were done by a rater watching 6 min of interaction from the posttest sessions, 2 min of introduction to DCCS, 2 min of story retell, and 2 min of HSKT. The rater was blind to the intervention of a specific child. The scores for the 7 behaviours were combined and divided by the maximum score of 21 ([name] & [name], Language and executive functions in Swedish preschoolers: a pilot study, submitted).

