### Hypotheses

On the basis of findings in earlier studies, we formulated seven sets of hypotheses corresponding to each of the seven research questions. The study aims to address the research questions by testing each of these hypotheses, listed in Table 1 below. For each hypothesis, Table 1 shows the outcome variable that is hypothesized to be affected, the intervention(s) or predictor either to affect or to be correlated with that outcome variable, the kind of effect or relationship that the hypothesis involves, for research questions 3 and 4, the mediating or moderating variables, the measure(s) used to estimate the outcome variable of the hypothesis at hand, and, finally, the kind of analysis method that will be conducted in order to test the hypothesis. In the following sections, we describe the method, the study design, the measurements and the analyses that will be used to test these hypotheses.

**Table 1 Tab1:** Hypotheses corresponding to each of the seven research questions described in terms of the affected outcome variable, the affecting intervention(s) or correlated predictor, the effect or relationship type, the mediating or moderating variable (if applicable), and analysis method used for hypothesis testing

Research question	Outcome variable(s)	Intervention/ Predictor	Effect	Mediator / moderator	Measure(s)	Analysis
RQ1: Intervention effects	EF	SEMLA & DIL	Positive intervention effects	–	Selective attention difference, EF indice difference	Mixed effects modelling
	Early Maths skills	SEMLA & DIL	Positive intervention effects	–	Maths difference	Mixed effects modelling
	Socioemotional skills	SEMLA & DIL	Positive intervention effects	–	TEC difference	Mixed effects modelling
	Communication	SEMLA & DIL	Positive intervention effects	–	Communication indice difference	Mixed effects modelling
	Language	SEMLA & DIL	Positive intervention effects	–	Language indice difference	Mixed effects modelling
RQ2: Intervention differences	Maths	SEMLA vs. DIL	Stronger effect of DIL	–	Maths difference	Planned comparisons
	EF	SEMLA vs. DIL	Differential effect	–	Selective attention difference, EF indice difference	Planned comparisons
	Communication	SEMLA vs. DIL	Stronger effect of SEMLA	–	Communication indice difference	Planned comparisons
	Language	SEMLA vs. DIL	Stronger effect of SEMLA	–	Language indice difference	Planned comparisons
RQ3: Mediating effects	Socioemotional skills	SEMLA & DIL	EF mediated effect	EF	TEC difference	Test of mediation effect

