### Composite measures

Three composite measures were used to assess general EF, language ability, and communicative ability. These composite measures were calculated by summing the standardized individual component scores, and then standardizing the resulting sum scores. The EF composite measure consists of the individual DCCS, Flanker, HSKT, and FDS components, the language composite measure consists of the individual PPVT, Predicates, Subordinates and Events components, and the communication composite score consists of the individual TEC, and the scores from a blind rater on communicative skills measured from the video-recordings of the test situation.

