### RQ1 analyses: Intervention effects

For RQ1 hypotheses, mixed effects modelling will be used to test the null hypotheses that there are no intervention effects on each of the respective outcome variables. Mixed effects modelling allows for the inclusion of multiple hierarchically nested random effects, such as children nested within preschool units and preschool units nested within preschools (e.g., [100]). The mixed effects model can thereby account for systematic influences of preschool units or preschools on the outcome variables. The model formula for the RQ1 hypothesis analyses is:

$$ {\mathrm{POSTSCORE}}_{\mathrm{ijk}}=\kern0.5em {\upalpha}_{0\mathrm{jk}}+{\upalpha}_{00\mathrm{k}}+{\upbeta}_1{\mathrm{INTERVENTION}}_{0\mathrm{jk}}+{\upbeta}_2{\mathrm{Y}}_{\mathrm{ijk}}+{\upbeta}_3{\mathrm{PRESCORE}}_{\mathrm{ijk}}+{\upbeta}_4{\mathrm{FIDELITY}}_{\mathrm{ijk}}+{\upbeta}_5{\mathrm{ECERS}}_{00\mathrm{k}}+{\upvarepsilon}_{\mathrm{ijk},}\ {\upvarepsilon}_{\mathrm{ijk}}\sim \mathrm{N}\left(0,{\upsigma^2}_{\upvarepsilon \mathrm{ijk}}\right),{\upalpha}_{\mathrm{j}}\sim \mathrm{N}\left(0,{\upsigma^2}_{\upalpha \mathrm{j}}\right),{\upalpha}_{\mathrm{k}}\sim \mathrm{N}\left(0,{\upsigma^2}_{\upalpha \mathrm{k}}\right) $$

In the models, the *i*th child is nested within the *j*th preschool unit, which in turn is nested within the *k*th preschool.

These models predict the postscore of the given outcome measure for child *i* as a function of the intervention administered at preschool unit *j*, using the control intervention as the baseline category. They also control for the set of background variables Y of child *i*, as well as the prescore measure of child *i*, centered around zero, as well as the fidelity score for child *i*, as explained in more detail above. Further, they control for the total ECERS rating of preschool *k*, thereby taking into account any influence of preschool quality on the outcome variables. Finally, they include individual intercepts α for each preschool *k*, as well as individual intercepts α for each preschool unit *j*, thereby controlling for systematic differences between preschool units and preschools with respect to the outcome variables.

Separate models will be conducted on selective attention, early maths skills and emotional comprehension, as well as on the composite measures of EF, language and communication.

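### The communication rating is described at posttest only, so the composite has no like-for-like pretest value for the planned difference and PRESCORE analyses; TEC, half of the composite, also carries its own effect into the communication result.

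*Protocol article*

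**What the plan says.** **The rating.** Under Measures of communication, seven behaviours are each scored 0 or 1 from video. "The ratings were done by a rater watching 6 min of interaction from the posttest sessions", made up of "2 min of introduction to DCCS, 2 min of story retell, and 2 min of HSKT". On scaling: "The scores for the 7 behaviours were combined and divided by the maximum score of 21". No rating of pretest video is mentioned.

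**The composite.** Under Composite measures, "the communication composite score consists of the individual TEC, and the scores from a blind rater". Composites are "calculated by summing the standardized individual component scores, and then standardizing the resulting sum scores", so the two parts carry equal weight. TEC is also analysed alone as the measure of socioemotional skills.

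**The analyses.**
- Table 1 gives "Communication indice difference" as the measure for communication in RQ1, RQ2, RQ3, RQ4 (moderation by ECERS) and RQ7. For RQ5 it lists the composite without a difference.
- The RQ1 model contains PRESCORE and is to be fitted to selective attention, maths and emotional comprehension, "as well as on the composite measures of EF, language and communication".
- The RQ4-ECERS model contains PRESCORE and names the communication score.
- The RQ5 model contains an intervention by TIME interaction and is also to be fitted to communication.
- RQ7 compares the variance of pre-post difference scores between SEMLA and DIL.

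**The concern.** A difference or a prescore needs the same quantity at both times. If the rating exists only at posttest, the posttest composite has two parts and a pretest composite could have only TEC. The analyst would then have to choose, after data collection, what stands in for the communication baseline. The article says its procedures were fixed before analysis to guard against result fishing, and this gap works against that aim.

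The second issue is interpretation. TEC and communication are tested as separate outcomes in RQ1, RQ3, RQ4-ECERS, RQ5 and RQ7, although one contains the other. RQ2 is the sharpest case. Table 1 lists no SEMLA-vs-DIL hypothesis for socioemotional skills, but it does predict a stronger SEMLA effect on communication. A SEMLA advantage confined to TEC would therefore count towards a claim about communication.

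**Working it through.** **1. What the score is built from.** The stated maximum is 21. Seven behaviours × three clips × 1 point = 21, which reproduces it exactly. The three clips are the ones described as posttest material, so the whole score range is accounted for by posttest footage.

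**2. Which analyses need a pretest value for communication.**

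| Analysis | Table 1 measure | Method text | Affected? |
|---|---|---|---|
| RQ1 | difference | postscore with PRESCORE | yes |
| RQ2 | difference | compares postscores, but Power calculations tie it to the RQ1 models | through RQ1 |
| RQ3 | difference | regression equations without a prescore | Table 1 label only |
| RQ4-ECERS | difference | postscore with PRESCORE | yes |
| RQ5 | composite, no difference | model with TIME | TIME term only |
| RQ7 | difference | variance of difference scores | yes |

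**3. How much of a TEC effect passes into the composite.** Let r be the correlation between TEC and the rating. The documents do not give it; 0 to 0.5 is assumed. For a standardised sum of two standardised parts:
- correlation of the composite with TEC = √((1 + r)/2): 0.71 at r = 0, 0.87 at r = 0.5;
- composite shift when only TEC moves by d = d/√(2 + 2r), a fraction of 1/√2 = 0.71 at r = 0 and 1/√3 = 0.58 at r = 0.5.

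Table 3 assumes TEC effects of 0.1 (control), 0.2 (DIL) and 0.6 (SEMLA). With no effect on the rating:
- SEMLA vs control, d = 0.6 − 0.1 = 0.5: 0.5/√2 = 0.35 SD to 0.5/√3 = 0.29 SD;
- SEMLA vs DIL, d = 0.6 − 0.2 = 0.4: 0.4/√2 = 0.28 SD to 0.4/√3 = 0.23 SD.

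**4. How often such a shift would be significant.** Inputs from the article: 432 children in 28 units (mean 15.4) and a smallest arm share of 32%, so 0.32 × 432 ≈ 138 per arm; alpha 0.05, taken as two-sided. Assumed: intracluster correlation (ICC) 0 to 0.10, pre-post correlation 0 or 0.5. The calculation uses a normal approximation with 138/(1 + 14.4 × ICC) effective children per arm and SD √(1 − ρ²), where ρ is the pre-post correlation.

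| Contrast | Lowest (r = 0.5, ICC 0.10, ρ = 0) | Highest (r = 0, ICC 0, ρ = 0.5) |
|---|---|---|
| SEMLA vs control | 0.34 | 0.92 |
| SEMLA vs DIL | 0.23 | 0.77 |

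These are before false-discovery adjustment. With the rating alone and no effect on it, the figure is 0.05.

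The article's own TEC power in Table 4 comes from simulation on pilot data that are not shown, so a formula cannot verify it. Tables 3 to 7 contain no entry for communication, so no stated power figure changes.

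**The case against.** **The pretest material probably exists.** Under Behavioural testing, children were tested in both periods, sessions were video-recorded partly to capture verbal and nonverbal interaction, and the three rated tasks were run both times. The section on the measure does not say that only posttest video was rated. A reader might infer that the outcome cannot be analysed at all; the article does not support that. It may contain one incomplete sentence, or a rating may be missing, and the text does not settle which. The conflict between sections stands either way.

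**The reach is uneven.** RQ5 in Table 1 uses no difference, the RQ3 equations use no prescore, and the RQ2 text compares postscores. The difference label in Table 1 fits the postscore models loosely for every outcome, not only communication. This is accepted and reflected in the table above. The conflict remains in full for RQ1, RQ4-ECERS and RQ7.

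**TEC in the composite is a disclosed choice.** If TEC truly changes, the composite truly changes, so rejecting its null is not a false positive. This also stands. A reader might go further and infer that a TEC effect will necessarily be reported as a communication effect, or that entering TEC twice damages the false-discovery procedure. Neither is shown. Significance depends on correlations and an ICC that the article does not give, and no inflation of the error rate has been demonstrated. What remains is that the label communication can rest on TEC alone.

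**Conclusion.** The point holds as an internal conflict. The communication rating is described from posttest sessions only, while Table 1, the PRESCORE terms in RQ1 and RQ4-ECERS, the TIME term in RQ5 and the RQ7 variance test presuppose a pretest value. This rests on the text alone and needs no assumption. It affects one of the six modelled outcomes and can be repaired.

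The TEC overlap is secondary and concerns interpretation. Its size, 58% to 71% of any TEC effect, follows from the equal weighting and an assumed component correlation of 0 to 0.5. The shifts in SD units also require the Table 3 effects, which are simulation inputs, not results. They are expected shifts in the estimate and do not predict a significant finding.

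**What to change.** **If pretest clips were rated, or can be rated from the existing recordings by the same blinded rater:** correct Measures of communication to say so and use that rating in the prescore. This keeps the difference, the PRESCORE models and RQ7. The cost is rater time if the clips are not yet scored. The retell story differs between pretest and posttest, which should be noted where differences are read as change.

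**If not:**
- analyse the blind rating as a posttest-only outcome in the RQ1/RQ2 and RQ4-ECERS mixed models, with the EF, language and TEC prescores already collected as baseline covariates;
- delete the word difference for communication in Table 1;
- fit RQ5 for communication without the TIME interaction;
- drop communication from RQ7.

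The cost is some precision compared with a true prescore, and one variance test.

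**In either case:** judge the communication hypotheses, above all the SEMLA-vs-DIL hypothesis in RQ2, on the blind rating alone. At the least, report the rating beside the composite before claiming any communication effect. Because data collection has ended, record any change to the composite as a dated amendment made before analysis.
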